### Inclusion criteria

Adolescents (ages 13 through 18) experiencing elevated levels of depressive symptoms on the Center for Epidemiologic Studies Depression (CES-D; [50]) scale are eligible for the study (eligible scores are between 8 to 17, inclusive, on the ten-item shortened scale; those with scores of 18 to 20 are considered with permission of the principal investigator). Adolescents also are included if they have a past history of depression or dysthymia.

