### Exclusion criteria

Adolescents must not have any of the following: (a) a current DSM-IV diagnosis (Kiddie Schedule of Affective Disorders [K-SADS]; [52]) of Major Depressive Disorder, current therapy for depression, or be taking antidepressants (for example, SSRIs, TCAs, MAOIs, bupropion, nefazodone, mirtazapine, or venlafaxine); (b) a history of being treated with Dialectical Behavioral Therapy or eight or more sessions of Cognitive Behavioral Therapy; (c) a current CES-D score of outside the range of 8 to 20 on the short form or 16 to 35 on the long form [50]; (d) a DSM-IV diagnosis of schizophrenia (current or past) or bipolar disorder; (e) a current serious medical illness that causes significant disability or dysfunction; (f) a significant reading impairment (a minimum sixth-grade reading level based on parental report), mental retardation, or developmental disabilities; (g) a serious imminent suicidal risk (as determined by endorsement of current suicidality on the CES-D or in the K-SADS interview) or other conditions that may require immediate psychiatric hospitalization; (h) psychotic features or disorders, or currently be receiving psychotropic medication; or (i) extreme, current drug/alcohol abuse (greater than or equal to 2 on the CRAFFT Screening Test; [53]).

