### Randomization

Participants are assigned randomly to CATCH-IT or HE. Randomization was determined by a computer generated sequence and was blocked by practice and time of entry, and stratified by level of risk severity (based on CES-D score, prior episodes of either major depression or dysthymia), age (13 to 14 or 15 to 18) site (Chicago or Boston) [56,57].

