##### Phone screen interview

The phone screen is a 10- to 15-minute scripted interview developed by study staff and conducted over the phone with the adolescent (those who screened positively on the two-question screener or who contacted the study team in response to a letter about the study from their pediatrician). After parental permission and assent (or consent for those age 18) are provided, adolescents are then asked about the presence of exclusion criteria. This includes a checklist of disqualifying characteristics (a sample item is “Are you currently in counseling for depression?”) and a subsequent depression symptom checklist, to screen for adolescents who meet criteria for current major depressive disorder (five or more symptoms; A sample item is “Has there been a 2-week period of time in the past 2 months when you have been feeling down, depressed, or sad much of the time?”). Adolescents who do not endorse these preliminary exclusion criteria are then administered the short, ten-item version of the CES-D (see description below) to assess current depressive symptoms; scores above 20 are excluded from the study and given referral to treatment, and scores of 8 to 20 (18 to 20 on a case-by case basis) are eligible for the in-person K-SADS interview (where final eligibility for the study is determined), and scores below 8 are provided with a final three question screen for past depressive episode (a sample item is “Has there ever been a time in your who life when for at least 2 weeks, you felt down, depressed, or sad for much of the time?”). Those who scored below 8 on the short CES-D but endorse a positive history of depressive episode are eligible for an in-person K-SADS interview, and those who do not are excluded.

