### Statistical analysis

#### Survival analyses

Preceding the main analysis of whether the rate of MDD onset varies by intervention condition, we will test for constant hazard over time. If this test is not significant at 0.10 will use Cox proportional hazards, adjusted for age and sex, to compute the hazard ratio for adolescent major depressive episodes for the intervention group in comparison to the HE group. We will also test whether time to MDD depends on the interaction of intervention condition by baseline level of symptoms. If the test or diagnostics reveal nonproportional hazards (that is, there is evidence of differential effect over time), we will include this nonproportionality in analyses. We have used such limited “model fitting” tests without regard to the magnitude of intervention effect in previous analyses that still preserve the Type I error rate [97], and will follow multiple comparison procedures we have used previously to identify time intervals where significant effects are found [88].

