#### Mediator analysis

In addition to examination of whether the intervention impact varies as a function of baseline symptoms, we will evaluate potential mediators including change in adolescent motivation, principles (intervention experience characteristics) of effective preventive interventions (adherence/dose, positive relationships, training and socio-cultural relevance, as reported by the adolescent) and changes in adolescent vulnerability and protective factors (social support, automatic negative thoughts, depressed mood). Based on our recent work on a comparison of analytic models for mediation with nonlinear models [113], we will use the “product of coefficients” method to conduct tests of mediation and the bootstrap method for accurate confidence intervals [114]. To examine the effects of adolescent participation with the website, we will conduct complier average causal effect (CACE) analyses that include covariates predicting participation status [115-118].

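### The entry rule links symptom level to past depression, and the planned arm-by-symptom test names no history term, so an effect difference by history may be partly reported as one by symptom level

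*Protocol article*

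**What the plan says.** All references are to the Protocol article.

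- **Survival analyses.** For the main hazard ratio the authors "will use Cox proportional hazards, adjusted for age and sex". The next sentence adds the interaction test: "We will also test whether time to MDD depends on the interaction of intervention condition by baseline level of symptoms". Mediator analysis refers again to "examination of whether the intervention impact varies as a function of baseline symptoms".
- **Inclusion criteria.** By symptoms, "eligible scores are between 8 to 17, inclusive, on the ten-item shortened scale", with 18 to 20 admitted by permission. By history, "Adolescents also are included if they have a past history of depression or dysthymia".
- **Phone screen interview.** "Those who scored below 8 on the short CES-D but endorse a positive history of depressive episode are eligible for an in-person K-SADS interview". Those below 8 who report no such episode are excluded.
- **Exclusion criteria (c).** This removes anyone with "a current CES-D score of outside the range of 8 to 20 on the short form or 16 to 35 on the long form". It makes no exception for history.
- **Randomization.** Allocation is "stratified by level of risk severity (based on CES-D score, prior episodes of either major depression or dysthymia" (with age group and site), so CES-D score and prior episodes both have to be known before randomisation.
- **Moderator analysis.** Subgroups by level of risk are planned. Prior episode is not named there.

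**The concern.** Admission on symptoms or history ties the two together. At the phone screen everyone below 8 has a reported past episode, and above 8 only some do. If CATCH-IT works better or worse in adolescents with a past episode, and symptom level itself does not matter, the average effect still differs between low and high scorers. A model with arm, symptoms and their product, and no history terms, will attribute part of that difference to symptoms.

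Baseline symptom level is the one effect modifier named with the main survival analysis, and aim (d) in Background asks for whom the programme works. A conclusion about symptom level that really reflects history could point later users of the programme to the wrong group. Part of the symptom-history link comes from this trial's entry rule, so such a conclusion need not carry over to settings without that rule.

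**Working it through.** **Inputs from the article (Sample size analysis):** 200 per arm; 72% of controls free of depression at one year, exponential through year two; hazard ratio 0.62; attrition 7% per quarter in year one and 2% per quarter in year two. Two-sided 5% is assumed, because alpha is not stated.

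**Step 1: reproduce the stated power.** The control hazard is -ln(0.72) = 0.3285 per year, and the intervention hazard is 0.62 x 0.3285 = 0.2037. Over eight quarters with dropout at quarter end, expected events are 135.3. Power = Φ(√135.3 x |ln 0.62|/2 - 1.96) = Φ(11.63 x 0.239 - 1.96) = Φ(0.82) = 0.794. With dropout spread within the quarter, events are 131.8 and power is 0.784. Both agree with the stated 80%, so these rates are a sound base for simulation. The article gives no figure for the interaction test.

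**Step 2: strength of the link.** Let f be the share entering below 8 and p the share with a history among the rest. The overall history share is H = f + (1-f)p. The correlation between scoring below 8 and having a history is √[f(1-p)/H]. The article gives neither f nor p.
- f = 0.15, p = 0.30: H = 0.405, correlation √(0.105/0.405) = 0.51.
- f = 0.35, p = 0.15: H = 0.4475, correlation √(0.2975/0.4475) = 0.82.

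**Step 3: first-order size.** Suppose the log hazard ratio depends on history only. Below 8 it equals the value with history. At 8 or more it is roughly a mixture with weights p and 1-p. The apparent difference between low and high scorers is then about (1-p) times the true difference by history.
- HR 0.9 versus 0.5: ln(0.9/0.5) = 0.588; times 0.85 or 0.70 gives 0.50 or 0.41.
- HR 0.45 versus 0.9: ln(0.9/0.45) = 0.693; times 0.85 or 0.70 gives 0.59 or 0.49.

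Symptoms have no effect of their own here, yet the log hazard ratio appears to differ by 0.41 to 0.59 between the two score groups.

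**Step 4: rejection rate of the planned test.** Cox simulation with N = 400, the attrition above and 600 runs per setting. Assumed: p of 20% or 40%, the 72% rate applied to adolescents without a history, and a hazard 1.5 times higher with one. The phone score is taken as the baseline score. Ranges cover both values of p and, in the moderate column, both directions of the difference.

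| Share below 8 | Common HR 0.62 | HR 0.45 and 0.85 by history | HR 0.30 without, 1.00 with history |
|---|---|---|---|
| 0% | 6.2-6.3% | 5.2-6.3% | 4.5-5.7% |
| 10% | 5.2-5.3% | 6.7-10.8% | 12.3-25.2% |
| 20% | 6.0-6.3% | 9.0-17.2% | 24.5-41.8% |
| 30% | 5.5-6.0% | 10.8-18.5% | 26.5-53.8% |
| 40% | 4.3-5.7% | 13.8-25.3% | 33.2-56.3% |

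The simulation error at 5% is √(0.05 x 0.95/600) = 0.9 points. For shares of 10-40%, the correlation between score and history is -0.23 to -0.67. The mean spurious interaction in the moderate column is 0.08 to 0.22 log-HR per SD of the score.

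At f of 15-35%, p of 15-30% and HR 0.9 versus 0.5 or 0.45 versus 0.9 by history, two further sets of runs gave 8-21% and 7-24%. I quote the wider range.

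**Step 5: with history in the model.** Adding prior episode and arm by prior episode brings rejection of the symptom interaction to 2.8-6.3% over every cell of the table, and to about 3-6% in the further runs. The standard error of the symptom interaction rises by about 3-38%.

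**Step 6: baseline score not equal to phone score.** At an assumed correlation of 0.6 between the two, rejection by the planned test falls to 6-15%.

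**The case against.** A reader might infer that every adolescent with low baseline symptoms has a past episode, and that a history effect will be reported as a symptom effect. The documents do not support that, for three reasons.

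- **The below-8 route is contradicted.** Exclusion (c) closes it with no exception for history. If nobody enters below 8, the link made by the entry rule disappears and the test stays near 5%.
- **The rule applies to the phone score.** Participants complete further scales at the enrolment assessment, and the CES-D under Instruments is the 20-item form. An adolescent without a history who scored 8 or more by phone can score low at baseline. The link is then weaker, though not gone while the two scores correlate.
- **The error needs a true difference by history.** The documents give no evidence of one, and with a common effect the test holds its level. Even at 7-24%, most such trials would not declare symptom modification.

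Two further objections have some force. Age and sex are stated for the main hazard ratio; the covariates of the interaction model are not given, and a fuller plan may already include history. Also, the interaction validly describes how the effect varies over symptom levels among those enrolled. It misleads only when read as modification by symptoms themselves, but aim (d) invites that reading. The level-of-risk subgroups do not clearly answer the point, since no joint model of symptoms and prior episode is described.

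**Conclusion.** The concern holds in a conditional form. Under the route in Inclusion criteria and Phone screen interview, phone-screen symptom level and history are linked by design, and the stated test does not separate them. If the effect truly differs by history, part of that difference may be reported as one by symptom level.

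The size is roughly 7-24% rejection at a nominal 5%. It rests on assumed shares and hazard ratios that the article does not give, and on the phone score serving as the baseline score. The confounding is partial: entrants at 8 or more include adolescents with and without a history, which is why a joint model can separate the two. The point limits how a moderator result can be interpreted. It does not touch the main randomised comparison.

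**What to change.** 1. Keep the planned arm-by-symptom test, but base any conclusion about symptom level on a model that also contains prior episode and arm by prior episode. Prior episode feeds the randomisation strata, so it is already recorded.
2. As a check, report the symptom interaction among entrants with a phone-screen score of 8 or more, where adolescents with and without a history both occur.
3. State whether baseline symptom level means the phone-screen score or the score at the enrolment assessment.
4. Reconcile Inclusion criteria and Phone screen interview with exclusion (c), and report how many participants entered below 8.

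The cost is two model terms and a wider interval for the symptom interaction: about 1.03 to 1.38 times as wide, depending on the share below 8. No new data are needed.

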#### Longitudinal data analysis

We test the hypothesis that the intervention affects the course of depressive symptoms and other measures across time. Our general method will be to use growth curve modeling with continuous outcomes to examine how the intervention changes adolescent depressive symptoms, vulnerability factors, educational impairment, and quality of life. Simple comparisons will be calculated as appropriate (for example, number of depressed days [98]), and survival curve modeling will be used for binary outcomes for prevalence of disorders [44,99-103]. Guided by our methods development on growth models, we will address missing data using full information maximum likelihood and multiple imputation, which provide improvement over “last observation carried forward” and other less refined methods [104-106]. We will also examine whether or not there are variations in growth trajectories by introducing covariate interactions and mixtures to growth models, techniques that we and our colleagues have developed [97,107-110]. These more complex models can characterize quantitatively differential response, as well as qualitative changes, such as recurrence [111]. All such models will be preceded by careful model checking [67,93,107,112].

#### Mediator analysis

In addition to examination of whether the intervention impact varies as a function of baseline symptoms, we will evaluate potential mediators including change in adolescent motivation, principles (intervention experience characteristics) of effective preventive interventions (adherence/dose, positive relationships, training and socio-cultural relevance, as reported by the adolescent) and changes in adolescent vulnerability and protective factors (social support, automatic negative thoughts, depressed mood). Based on our recent work on a comparison of analytic models for mediation with nonlinear models [113], we will use the “product of coefficients” method to conduct tests of mediation and the bootstrap method for accurate confidence intervals [114]. To examine the effects of adolescent participation with the website, we will conduct complier average causal effect (CACE) analyses that include covariates predicting participation status [115-118].

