### Control group: health education

Health Education (HE) is an attentional control. This Internet site comprises 14 modules, 13 of which provide instruction on nutrition, safety, and other teen health and wellness topics. The 14th module discusses mood and seeking mental health treatment, and also addresses stigma and negative attitudes toward the treatment of mental disorders, as these have previously been identified as barriers to seeking and adhering to treatment [47,67]. Module 14 does not provide instruction in Behavioral Activation, Cognitive Behavioral Therapy, or Interpersonal Therapy. The HE Internet site does not include interactive elements such as videos, question prompts, or feedback on mood or progress.

The HE components are similar to those employed in previous primary care-based quality improvement/Chronic Care Model Interventions, incorporating patient psychoeducation, active monitoring and referral, with routine contact with a primary care provider. The HE group receives the same assessments as the CATCH-IT group (including notification and referral to mental health services) and routine contact with their primary care provider (PCP; estimated two to three visits per year), and also incorporates a parent Internet program that provides similar psychoeductional content about general adolescent health. Psychoeducation Internet site use is monitored to compare with use of the CATCH-IT intervention as an attentional control. Self-harm risk is managed based on a standard protocol.

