##### Physician Relationship Scale

The Physician Relationship Scale [33] contains nine items rating the participant’s relationship with his/her provider in understanding, engagement, helpfulness, comfort, and trust. Only adolescents in the CATCH-IT condition are administered this measure. This self-report measure is rated on a five-point Likert scale (1 = *strongly disagree* to 5 = *strongly agree*). A sample item is, “I trust my physician.” Higher scores reflect a more positive relationship with the provider. In our pilot study, Cronbach alpha was .85 [5,33].

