##### Perceived benefits of cognitive behavioral principles

Perceived benefits of the cognitive behavioral principles taught in the intervention are measured by five questions, which are rated by adolescents on a ten-point Likert scale (1 = *very unhelpful* to 10 = *very helpful*), with higher scores indicating a stronger perceived benefit for learning cognitive behavioral therapeutic techniques [92]. A sample item is, “change my behaviors in ways that have improved my mood.” In our pilot study, Cronbach alpha was .92 [5,33].

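### The provider-relationship scale is given in the CATCH-IT arm only, so it cannot support the planned mediation test or the planned moderator interaction

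*Protocol article*

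**What the plan says.** Under Statistical analysis, Mediator analysis, the protocol article lists a group of mediators that describe the adolescent's experience of the intervention: "principles (intervention experience characteristics) of effective preventive interventions (adherence/dose, positive relationships, training and socio-cultural relevance, as reported by the adolescent". For the method it states: "we will use the “product of coefficients” method to conduct tests of mediation and the bootstrap method for accurate confidence intervals". Under Moderator analysis, item (d) of the eight domains is the adolescent's relationship with the provider, to be examined by subgroup analyses and tests of interaction.

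Under Instruments, Relationships, the Physician Relationship Scale "contains nine items rating the participant’s relationship with his/her provider in understanding, engagement, helpfulness, comfort, and trust". The same paragraph adds: "Only adolescents in the CATCH-IT condition are administered this measure".

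The section Control group: health education says that HE adolescents get the same assessments as the CATCH-IT group. It also says that they have "routine contact with their primary care provider (PCP; estimated two to three visits per year".

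On training, the article describes a usability and clarity scale and two perceived-benefit scales, none with a stated arm restriction. The first perceived-benefit scale is introduced as follows: "Perceived benefits of the cognitive behavioral principles taught in the intervention are measured by five questions". The second does the same for interpersonal principles. Of the HE site's one module on mood, the article says: "Module 14 does not provide instruction in Behavioral Activation, Cognitive Behavioral Therapy, or Interpersonal Therapy". The other 13 HE modules cover general health topics.

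**The concern.** A product-of-coefficients test multiplies the effect of arm on the mediator by the effect of the mediator on the outcome given arm. The first factor is a comparison between arms, so the mediator must be measured in both. An arm-by-moderator interaction has the same requirement. A scale given in one arm only meets neither.

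The consequence falls on aim (d). Once the data are in, the only thing that can be estimated from this scale is whether CATCH-IT adolescents who rate their provider well also do better. That association could be reported as mediation or moderation, although it involves no randomised contrast and may simply reflect milder symptoms or higher motivation at entry.

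This cannot be left to a later analysis plan. It is a data-collection rule, and no analysis can recover scores that were never collected in one arm.

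**Working it through.** **Inputs.** Planned size is 200 per condition, 400 in all (Sample size analysis). Arm coverage of the Physician Relationship Scale is CATCH-IT only, so there are 0 HE observations. The test is product of coefficients with a bootstrap interval (Mediator analysis). Missing-data handling is full information maximum likelihood and multiple imputation, stated for the growth models (Longitudinal data analysis). No figure in the article is disputed, so the check is one of identifiability.

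**Step 1: the mediation models.** Let A be arm (1 = CATCH-IT, 0 = HE), M the mediator and Y the outcome.

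- a-path: M = i₁ + a·A
- b-path: Y = i₂ + c′·A + b·M
- mediated effect: a × b

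The rank of each design matrix, checked at 200 per arm, was:

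| M observed in | n | a-model rank | b-model rank |
|---|---|---|---|
| both arms | 400 | 2 of 2 | 3 of 3 |
| CATCH-IT only | 200 | 1 of 2 | 2 of 3 |

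With CATCH-IT data only, A equals 1 for everyone and duplicates the intercept. Neither a nor the direct effect c′ has an estimate. The slope b within CATCH-IT can still be computed, but there is nothing to multiply it by. A bootstrap resamples the same one-arm data and inherits the problem.

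**Step 2: the moderator model.** Y = j₀ + j₁·A + j₂·M + j₃·A·M. With M observed only where A = 1, the column A equals the intercept and the column A·M equals M. Two distinct columns remain of four, so j₃, the interaction, is not estimable.

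**Step 3: can the missing-data methods repair it?** No. The HE mean of M is not informed by any observation, so an imputation model must assume it. For illustration, assume b = −0.3 and write a as the CATCH-IT mean minus the HE mean:

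| Assumed HE mean relative to CATCH-IT mean | a | a × b |
|---|---|---|
| 1 point lower | +1 | −0.30 |
| 0.5 lower | +0.5 | −0.15 |
| equal | 0 | 0 |
| 0.5 higher | −0.5 | +0.15 |
| 1 point higher | −1 | +0.30 |

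Both sign and size follow from the assumption and not from the data.

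**Step 4: the passages side by side.** The control-group section says that assessments are the same in both arms; the scale's own paragraph says that HE adolescents are not given it. Both cannot be right. The control-group section also expects two to three provider visits a year in HE, so questions about trust in and comfort with one's provider apply to those adolescents.

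**Step 5: the training scales.** The usability and clarity items ask whether a module was easy to use, understand and read, and HE has 14 modules. The sample items of the two perceived-benefit scales concern changing one's behaviour and expressing feelings to important people; an HE adolescent could answer them. If these scales are given in both arms, which the text allows, the rank is 2 of 2 and the a-path can be computed. What remains is that the perceived-benefit scales rate principles that CATCH-IT teaches and HE is not described as teaching.

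**The case against.** The strongest objection is that the Mediator analysis section names no instrument. The Relationships heading also holds sibling, parental-behaviour and family-conflict scales with no arm restriction, and a journal article may leave the link between mediator and scale to the full protocol or analysis plan. This stands to the extent that the mediation finding is conditional on the link. It carries limited weight, because the section describes these mediators as features of the intervention experience, and of the relationship instruments only the provider scale fits that description. It does not help the moderator test: item (d) there names the relationship with the provider, and only one instrument described measures it.

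A second objection is that the matter is secondary. That is correct. One of several mediators and one of eight moderator domains are affected, and the Cox analysis of depressive episodes does not depend on them.

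A reader might infer more: that the training mediator also lacks HE data, so that its mediation test cannot be run either. The documents do not support this. No arm restriction is stated for those scales, the control-group section says that assessments are the same, and the article is explicit where it does restrict a scale to one arm. The HE site is said to have no question prompts, which might mean that no ratings are collected at the end of its modules, but the article does not say so. Nor does it say that missing HE scores would be filled with a fixed value, so no harm should be argued from such coding.

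**Conclusion.** The point holds for the Physician Relationship Scale. Given in one arm only, it cannot enter a product-of-coefficients test or an arm interaction; all 200 planned HE participants, half of the 400, have no score by design. For the moderator this follows directly from the text. For the mediator it rests on one assumption, that positive relationships is scored by this scale, which the wording favours but does not fix. The contradiction between the scale's paragraph and the control-group section stands in either case.

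For training, the conclusion is confined to interpretation. An arm difference on the two perceived-benefit scales would largely show that one arm was taught the content and the other was not, and would be hard to read as a mechanism. The documents do not show that it is inestimable.

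The matter deserves correction because it bears on a stated aim and the remedy is cheap while recruitment continues. It does not threaten the primary result.

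**What to change.** 1. In the Physician Relationship Scale paragraph, remove the restriction and give the nine items to HE adolescents too: at baseline for new enrolees and at the remaining visits for those already enrolled. With 234 of 400 enrolled at the September 2014 status, 400 − 234 = 166 adolescents across both arms could still be measured from baseline. Reconcile the paragraph with the control-group section.
2. If the scale stays in one arm, remove it from the product-of-coefficients and interaction tests. Report it as an association within CATCH-IT, adjusted for baseline symptoms and motivation and labelled as association.
3. In the Mediator analysis section, state which scale and which arms supply each mediator. For the two perceived-benefit scales, state that an arm contrast reflects exposure to the taught content and is not by itself evidence of mediation.

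The cost of the first option is a short extra questionnaire for HE participants, with HE scores missing for visits already completed; analyses of the scale would have to state which visits and participants they cover. The second option costs only wording, but gives up the between-arm question for this construct.
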